### 7.3 LOST TO FOLLOW-UP

Given the shortness of the study observation it is highly improbable to have such events.

We only envisage a potential source of lost to follow-up of enrolled infants, consisting on early discharge/transfer to lower care unit (before 34 weeks) which is rather infrequent. In these cases, the research team are committed to contact the families/transfer hospital for a required study visit. Should the participant continue to be unreachable, he/she will be considered to have withdrawn from the study with a primary reason of lost to follow-up.

## 8 STUDY ASSESSMENTS AND PROCEDURES

### 8.1 EFFICACY ASSESSMENTS

The following sections describe all procedures and evaluations to be done as part of the study.

The specific timing of procedures/evaluations at each study visit is described in Section 1.2, Schema and Table.

#### 8.1.1 Study Visits Procedures

##### *8.1.1.1 Screening Visit*

During the Screening Visit, potentially eligible infants are screened for inclusion/exclusion within 0-72h of birth. Potential candidates for enrolment are infants with haemodynamic insufficiency in the first 72 hours after birth, born at less than 33 weeks gestation (echocardiography will be performed in the first 24h and every 10-12h during the first 72h after birth). Eligibility parameters (SVC flow <51 ml/kg/min) as well as other clinical and biochemical parameters are assessed if clinically indicated but not all of them will be recorded in the eCRF.

Strategies for recruitment outlined in section 5.4 and the informed consent process described in section 10.1.1 are followed during the screening and enrolment of patients into the study, using specially designed Informed Consent Documents (ICD).

##### *8.1.1.2 Enrolment: Baseline Visit*

If the inclusion criteria are met, and there are no reasons for exclusion, the infant is then enrolled into the trial and allocated to a dosage regimen according by the study statistician. At this point the Screening Visit finishes and the Baseline Visit parameters outlined in section 8.1.2.3 below are assessed.

The study intervention should be initiated straight away after the Baseline Visit always within the first 72 hours from birth.

#### *8.1.1.3 Treatment: Start of Dobutamine Infusion Visit*

For all dosage regimen, the study intervention is initiated with continuous infusion of the initial dose of dobutamine during the first treatment visit.

#### *8.1.1.4 Treatment: PD/PK Assessment Visit*

The patient PD response to the dobutamine treatment should be evaluated at 60 minutes from the start of effective dose infusion, to establish if the treatment success dose has been achieved. Blood sample (1 millilitre) will be taken.

Effective dose infusion is define as the time ( $t_0$ ) when the study medication enters blood stream, which is calculated according to the following equation:

$$t_0 = t_{\text{switch on}} + t_d$$

$$t_d (\text{min}) = (\text{volume (ml)} / \text{velocity (ml/h)}) \times 60 (\text{min/h}),$$

where *volume* refers to the catheter lumen plus the stopcock dead space and *velocity* refers to the summation of the infusion rate of all the infusions coming through the line. Dobutamine infusion should be at the stopcock closest to the catheter entry. Before dobutamine is connected to the stopcock, the whole system (including bionector) will be fed with the dobutamine solution and the pump will be switched on for a few minutes to ensure that no pulling out effect is added at start. The pump will be switched off and the system will be connected to the stopcock. Finally the pump will be switched on and the time will be registered ( $t_{\text{switch on}}$ )

The following criteria will be checked at every patient at the dose evaluation:

- Main response biomarker: SVC flow > 55 ml/kg/min

And other parameters:

- MABP increase by 20% (roughly 4-6 mmHg)
- Decreasing serum lactate levels
- Base excess levels being less negative
- CRT < 4 sec

Throughout the treatment, a series of clinical and biochemical parameters described in sections 8.1.2 below are evaluated and recorded in the eCRF according to the timings given in the section 1.3.

#### *8.1.1.5 Treatment: PD/ PK re-assessment Visit*

The patient PD response to the dobutamine treatment should be re-evaluated at 180 minutes from the start of infusion of the effective dobutamine dose (SVC flow above 55 ml /K/min). A second one millilitre of blood sample will be obtained.

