| PK assessments        | Samples for dobutamine will be taken at 60 min and 180 min after the allocated dose had time to enter the systemic circulation. In the case the targeted PD effect is reached with a different dose, the second PK sample will be withdrawn 180 min after effective dose infusion.                                                                                                                                                                                                                                                                                                                                                                                                                                                                                                                                                                                                                                                                                                                                                                                                                                                                                                                                                                                                                                                                                                                                                                               |        |        |        |        |        |        |                        |   |     |    |      |    |              |    |    |    |    |    |              |   |   |    |   |   |

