## 1.2 SCHEDULE OF ASSESSMENTS(SoA)

|                                                 |                                                      | Screening              | Enrolment          | Treatment: Dobutamine 5-7.5-10-12.5-15 µg/kg/min |                                     |                           | End of Treatment Assessment | Efficacy visit | Mid-term assessment | Long-term follow-up                         |
|-------------------------------------------------|------------------------------------------------------|------------------------|--------------------|--------------------------------------------------|-------------------------------------|---------------------------|-----------------------------|----------------|---------------------|---------------------------------------------|
| Study Visit:                                    |                                                      | Screening Visit (a)    | Baseline Visit (b) | Start Infusion                                   | PK/PD Assessment                    | PK/PD re-Assessment       | EoT Visit                   |                |                     |                                             |
| Time:                                           |                                                      | Within 0-72 h of birth |                    | 0 min                                            | 60 min after start of each infusion | 180 min of effective dose | At treatment completion     | At 72h         | W34-W38 PMA         | 24±4 months (age corrected for prematurity) |
| Signed Consent Form                             |                                                      | X                      |                    |                                                  |                                     |                           |                             |                |                     |                                             |
| Date /time recording                            |                                                      | X                      | X                  | X                                                | X                                   | X                         | X                           | X              | X                   | X**                                         |

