#### Pharmacokinetic and pharmacogenetic analysis:

Pharmacokinetic analysis will be performed for the complete study population. Differences between different groups and patients will be compared using Chi-squared Test. For all comparisons 95% CIs (two-sided) will be required.

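### The 180-minute echo and second PK sample are tied to the dose that worked in one place and to the allocated dose in another, so the 180-minute PK/PD data may be selected on response

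*Protocol*

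**What the plan says.** The protocol times the second PK/PD assessment in four places.

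- **Section 8.1.1.5 (re-assessment visit).** The response is to be "re-evaluated at 180 minutes from the start of infusion of the effective dobutamine dose (SVC flow above 55 ml /K/min", and a second 1-ml sample is drawn. The bracket defines the effective dose by its result.
- **Schedule of Assessments (section 1.2).** The re-assessment column is headed "180 min of effective dose", without saying what *effective* means. The preceding column is headed "60 min after start of each infusion" and carries no response condition.
- **Synopsis, PK assessments.** The default is unconditional: "Samples for dobutamine will be taken at 60 min and 180 min after the allocated dose had time to enter the systemic circulation". An exception follows: "In the case the targeted PD effect is reached with a different dose, the second PK sample will be withdrawn 180 min after effective dose".
- **Synopsis and section 3, primary endpoint.** The echoes are at 1 and 3 hours after effective infusion of the allocated dose.

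Section 8.1.1.4 takes an echo and a sample at 60 minutes "to establish if the treatment success dose has been achieved. Blood sample (1 millilitre) will be taken". It also defines effective dose infusion as t0, the time the drug enters the bloodstream, which has nothing to do with response.

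For the analysis, section 9.1.2 states "Pharmacokinetic analysis will be performed for the complete study population". The related secondary objective is to find what explains interindividual PK/PD variability, with the PK–PD correlation as its endpoint (section 3).

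**The concern.** In section 8.1.1.5, whether an infant has a 180-minute concentration–flow pair depends on the flow itself. Infants who never reach the target drop out of the 180-minute data. Infants titrated to response enter at a higher dose and a later clock time, both fixed by how they responded. Choosing observations by the outcome, and choosing the dose by the response, can each weaken an observed concentration–response relation. Infants with low exposure, or with adequate exposure and no effect, are among the most informative about variability, and they are the ones who may be missing.

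The 180-minute point is not redundant. Section 4.2 reports times to steady state of 15 to 180 minutes, so some infants are still accumulating drug at 60 minutes. A sample that was never drawn cannot be recovered by any later analysis plan, so the timing has to be settled in the protocol.

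**Working it through.** **1. The passages side by side**

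| Place | Anchor of the 180-minute measurement | Infant who never exceeds 55 |
|---|---|---|
| Synopsis, PK assessments | t0 of the allocated dose; moved if another dose reaches target | Sample due at 180 min |
| Synopsis and section 3, primary endpoint | Allocated dose (3-hour echo) | Echo nominally due, though failure is already known at 1 h |
| Schedule, re-assessment column | The effective dose, undefined there | No time, unless *effective* means t0 |
| Section 8.1.1.5 | The dose that gave flow above 55 | No time given |

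Read with section 8.1.1.5, the text for that visit, the Schedule follows the response-based sense. Read with section 8.1.1.4, it could mean t0. The two readings give different datasets.

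**2. The plan's own figure**

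Section 9.1.1 plans 5, 9, 12, 4 and 0 infants at 5, 7.5, 10, 12.5 and 15 micrograms/kg/min. The sum is 5 + 9 + 12 + 4 + 0 = 30, as stated. A one-parameter power CRM was simulated with the plan's efficacies as both truth and prior guesses, target 80% and cohorts of 3. It also assumed a start at the lowest dose, no skipping and prior variance 1.34. It gives 3.5 / 9.0 / 13.2 / 4.2 / 0.1, within 2 patients in every cell. The table is therefore a reasonable set of weights.

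**3. Infants without a 180-minute pair under section 8.1.1.5**

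Expected responders on the allocated dose = Σ n × efficacy.

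- Lower priors: 5×0.45 + 9×0.70 + 12×0.80 + 4×0.90 = 2.25 + 6.30 + 9.60 + 3.60 = 21.75 (72.5%), leaving 30 − 21.75 = 8.25.
- Upper priors: 5×0.50 + 9×0.75 + 12×0.85 + 4×0.95 = 2.50 + 6.75 + 10.20 + 3.80 = 23.25 (77.5%), leaving 6.75.

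If no failing infant reaches target on a later dose, 6.75 to 8.25 infants have no pair. If every failing infant is taken to 15 micrograms/kg/min, where the prior success is 95–100%, then 30 × (1 − 0.95) = 1.5 down to 30 × (1 − 1.00) = 0 have none.

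These counts treat the prior success rates as the chance of exceeding 55 at 60 minutes. If the rates describe reaching and maintaining the target, an infant who reaches it at 1 hour and loses it by 3 hours does have an effective dose, and the upper figures are then too high.

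**4. Timing for titrated infants**

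Take dose changes made immediately after each 60-minute assessment. By 180 minutes after the first t0, an infant has been on the new dose for at most 180 − 60 = 120 min after one step, or 180 − 120 = 60 min after two. Under section 8.1.1.5 the second pair instead falls at 60 + 180 = 240 min or 120 + 180 = 300 min after the first t0. The same visit label covers different clock times and doses.

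**5. Possible attenuation (illustration only)**

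A bivariate normal was simulated with an assumed true PK–PD correlation, keeping only the upper part of the PD distribution.

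| Assumed correlation | Top 72.5% kept | Top 95% kept |
|---|---|---|
| 0.3 | 0.22 | 0.27 |
| 0.5 | 0.38 | 0.46 |
| 0.7 | 0.57 | 0.66 |

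The assumed correlations are not in the protocol. The exercise truncates the same reading that is then correlated, whereas selection here acts on the earlier echo and flow at 180 minutes may fall again, so it probably overstates the loss from truncation. It leaves out the effect of titrating the dose to response. It concerns the 180-minute data alone.

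**The case against.** A reader might infer that 180-minute data exist only for responders, and that the whole PK/PD objective is therefore answered in a group chosen by its own outcome. The documents do not support that.

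- The synopsis default has no response condition, so on that text a never-responder keeps the second sample. The primary endpoint also nominally requires a 3-hour echo on the allocated dose.
- The 60-minute echo and sample apply to every infant before any selection, and the Schedule repeats that visit for each infusion. Those pairs can show low exposure, or exposure without effect.
- Buccal swabs are taken at enrolment (section 8.1.2.5), so genotype can be related to the 60-minute response in all infants.
- Sections 6.1.2 and 6.2.1 encourage up-titration first, so the number without any effective dose may be close to zero.
- Waiting 180 minutes on the dose being characterised is understandable given the reported times to steady state.

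All of this stands, and it limits the point to the 180-minute data. It does not remove it. The synopsis contradicts section 8.1.1.5 and does not override it. Nor does the synopsis say what a 180-minute sample represents after a dose change without response, or after a switch to rescue. The primary endpoint does not secure a 3-hour pair in non-responders either: an infant below target at 1 hour has already failed, and section 6.1.2 then leaves management to the physician. The same steady-state range that justifies a late sample also means the 60-minute pair is not a full substitute.

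**Conclusion.** The point holds as an internal contradiction with a possible selection effect. Section 8.1.1.5, and the Schedule read with it, condition the 180-minute echo and second sample on response. The synopsis and the primary endpoint place them on the allocated dose, and *effective* carries two meanings. If section 8.1.1.5 is followed, the 180-minute part of the PK/PD data is selected on its own outcome, contrary to the complete-population analysis in section 9.1.2.

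The expected number of infants affected by omission is 0 to 1.5 of 30 with full up-titration and 6.75 to 8.25 at most. This rests on the planned allocation, the prior success rates read as 60-minute rates, and 15 micrograms/kg/min as the top dose carrying a stated prior. Titrated infants add pairs at response-chosen doses in either case.

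It would go too far to conclude that the PK/PD objective is confined to responders, or that its result must be biased towards no relation. The 60-minute pairs are unaffected, and any attenuation figure is illustrative. The wording should be corrected, because data lost through the sampling rule cannot be restored at analysis.

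**What to change.** Reconcile the synopsis (PK assessments), the Schedule of Assessments and section 8.1.1.5, in line with the primary endpoint in section 3:

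1. Make the second sample and its paired echo due in every infant, whether or not the target was reached, at one stated time after one stated t0. The sponsor should choose the anchor and use it in all these places.
2. Record with each pair the dose running, the time since its last change and any rescue treatment.
3. Use *effective* in one sense only. If it stays attached to t0, call the dose that reached target something else.
4. State in section 9.1.2 that the PK/PD analysis uses all pairs, including the unselected 60-minute pair on the allocated dose, and that pairs obtained after titration to response are identified as such.

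No dosing or rescue rule needs to change. The cost is protocol wording, two or three recorded items, and, in a never-responder, a second 1-ml sample and a 3-hour echo, both of which the synopsis already plans.

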#### 8.1.1.6 Efficacy Visit

To test whether dobutamine alone achieved and maintained an acceptable haemodynamic status during the first 72 h from birth (secondary objective).

This study short-term efficacy outcome means that at 72h the infant is alive, and the clinical condition is:

- SVC flow > 55 ml/kg/min;
- MABP > GA;
- Decreasing serum lactate levels;
- CRT < 4s;
- Urine output > 1 ml/kg/h;
- Dobutamine alone was used (regardless the dose).

Investigators will be asked to report if, according to this definition, short-term success has been achieved or not. If not, investigators will also be asked to check if persistent circulatory failure or death is due to something different from pure transitional circulation adaptation, e.g., sepsis, haemodynamically significant PDA, air trapping (lung over distension), pneumothorax, pleural or pericardiac effusion.

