|                                                 | Pulse oximetry                                       | X*                     | X                  | X*                                               | X                                   | X*                        | X*                          | X              |                     |                                             |
|                                                 | Type of mechanical ventilation                       |                        | X                  | X                                                | X                                   | X                         | X                           | X              |                     |                                             |
|                                                 | Urine output                                         | X                      | X                  | X                                                | X                                   | X                         | X                           | X              |                     |                                             |
| primary outcome                                 |                                                      |                        |                    |                                                  | X                                   |                           |                             | X              |                     |                                             |
| Secondary outcomes                              |                                                      |                        |                    |                                                  |                                     |                           |                             |                | D                   |                                             |

X : Indicates Mandatory Procedures that should be entered into the eCRF;

X\*: Indicates data entered into the eCRF if available;

Pd\*: Indicates non-mandatory pharmacodynamics assessment at the visit that should be entered into the eCRF if available

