| 
 
To determine the individual variables that explain the interindividual pharmacokinetic (PK)/PD variability.
 
 | 
 
To determine the correlation between PK and PD.
 
 
[A] The effective start of the infusion (t0) will be calculated as the time at which the infusion pump is switched on plus the empirical value for the interval arising from the dead space. We summarize t0 as “the time at which dobutamine is expected to reach the circulation”
 
[B] Acceptable haemodynamic status is defined, for the purposes of this study, as the achievement and maintenance of dose success during the first 72 h from birth. The loss of such acceptable haemodynamic status occurs whenever there is a change in therapeutic strategy that involves cardiovascular treatment other than dobutamine alone due to exceeded safety parameters, treatment failure of the investigational infusion or the need for rescue treatment or death; any additional fluid bolus is considered as cardiovascular treatment.
 |
|---------------------------------------------------------------------------------------------------------------------------------------------------------------|----------------------------------------------------------------------------------------------------------------------------------------------------------------------------------------------------------------------------------------------------------------------------------------------------------------------------------------------------------------------------------------------------------------------------------------------------------------------------------------------------------------------------------------------------------------------------------------------------------------------------------------------------------------------------------------------------------------------------------------------------------------------------------------------------------------------------------------------------------------------------------------------------------------------------------------------------------------------------------|

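### The secondary 72-hour efficacy endpoint has two unreconciled definitions, and its clock starts at birth although infusion may start at any time up to 72 h

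*Protocol*

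**What the plan says.** **Definition 1.** Footnote [B], in the synopsis and in Section 3, defines acceptable haemodynamic status "as the achievement and maintenance of dose success during the first 72 h from birth". It then gives the loss rule: "The loss of such acceptable haemodynamic status occurs whenever there is a change in therapeutic strategy that involves cardiovascular treatment other than dobutamine alone". The stated grounds are exceeded safety parameters, treatment failure, need for rescue, or death, and any additional fluid bolus counts as cardiovascular treatment.

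**Definition 2.** Section 8.1.1.6 names the same secondary objective and says: "This study short-term efficacy outcome means that at 72h the infant is alive, and the clinical condition is". The list has SVC flow above 55 ml/kg/min, mean arterial pressure (MABP) above gestational age (GA), decreasing lactate, capillary refill time (CRT) under 4 s, "Urine output > 1 ml/kg/h", and use of dobutamine alone at any dose. This is the rule applied at the bedside: "Investigators will be asked to report if, according to this definition, short-term success has been achieved or not".

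**Analysis.** Section 9.1.2 analyses the proportion keeping an acceptable haemodynamic status over the first 72 h from birth. It points to neither definition.

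**Data and timing.** In the Schedule of Assessments, lactate at the 72-h visit is marked X*, which the legend explains as "Indicates data entered into the eCRF if available". Section 8.1.1.2 has infusion begin straight after the Baseline Visit, "always within the first 72 hours from birth". Section 8.1.1.1 repeats screening echocardiography every 10–12 h up to 72 h, so late entry is foreseen.

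**The concern.** One endpoint is described once as a history and once as a snapshot, with different conditions. The investigator's success report is collected under the snapshot, while the objectives table and the analysis text use the term defined by the history. The numerator therefore depends on which text the analyst follows. The denominator may too, because Section 9.1.2 excludes infants whose loss of status is confirmed to have a cause other than transitional adaptation, and who counts as having lost status differs between the definitions.

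Time at risk also differs between infants. One treated at 6 h must hold status for 66 h; one treated at 71 h is read out an hour later. With at most 30 infants, a few late entries or a few discordant scores would visibly move the reported proportion.

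**Working it through.** The protocol gives no expected rate or sample size for this endpoint, so there is no figure of the plan's to reproduce.

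**1. The definitions side by side**

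| Element | Footnote [B] | Section 8.1.1.6 |
|---|---|---|
| Form | Course over the first 72 h | State at 72 h |
| Alive, no other cardiovascular treatment | Yes, through the loss rule | Yes, at any dobutamine dose |
| SVC flow > 55 ml/kg/min | Through *dose success* (8.1.1.4, 8.1.1.5) | Yes |
| Decreasing lactate; CRT < 4 s | Only if *dose success* includes the other parameters of 8.1.1.4 | Yes |
| MABP > GA | No (8.1.1.4 has a 20% rise instead) | Yes |
| Urine output > 1 ml/kg/h | No | Yes |

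Section 8.1.1.6 therefore adds two criteria if *dose success* is read broadly, and four if it means SVC flow alone.

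**2. One infant, two answers**

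Take an infant of 28 weeks on dobutamine alone, with MABP risen from 20 to 25 mmHg, SVC flow 60 ml/kg/min, lactate falling, base excess less negative, CRT 3 s and urine output 1.5 ml/kg/h.

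- Rescue under Section 6.2.1 requires MABP below GA − 5 = 28 − 5 = 23, plus another sign. As 25 is not below 23, the trigger is not met. With no rescue given, status is not lost.
- The pressure rise is (25 − 20)/20 = 25%, so even the broad reading of *dose success* is satisfied. Under [B] this is a **success**.
- Section 8.1.1.6 requires MABP > 28. As 25 is not above 28, this is a **failure**.

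The same split can arise for any infant with MABP from GA − 5 to GA who has had no rescue. It also arises with MABP 30 mmHg and urine output 0.9 ml/kg/h. If lactate is not measured at 72 h, Section 8.1.1.6 cannot be scored unless another criterion has already failed.

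**3. Size of the gap between definitions (illustration)**

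Assume each of *k* extra criteria is met by a share *p* of [B] successes, independently. The ratio of 8.1.1.6 success to [B] success is then *p*^*k*.

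| | k = 2 | k = 4 |
|---|---|---|
| p = 0.90 | 0.90² = 0.81 | 0.90⁴ = 0.66 |
| p = 0.95 | 0.95² = 0.90 | 0.95⁴ = 0.81 |

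If [B] success were 24/30 = 80% (assumed), 8.1.1.6 success would lie between 0.80 × 0.656 = 52% and 0.80 × 0.9025 = 72%. Perfusion signs tend to move together. With complete correlation the ratio would rise to *p* itself, 90% (95%).

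**4. The clock**

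Time at risk is 72 − *s* for a start at *s* hours: 66 h for a start at 6 h, 48 h at 24 h, 24 h at 48 h, 12 h at 60 h, and 1 h at 71 h. The 180-min scan falls beyond 72 h when *s* + 3 > 72, so for *s* > 69. The 60-min scan does so for *s* > 71.

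For the loss rule in [B] alone, once status is achieved, assume a constant hazard set by a loss *L* over 66 h: *h* = −ln(1 − *L*)/66. The chance of no loss by 72 h is exp[−*h*(72 − *s*)].

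| Assumed L | s = 6 h | 24 h | 48 h | 69 h |
|---|---|---|---|---|
| 20% | 80% | 85% | 92% | 99% |
| 40% | 60% | 69% | 83% | 98% |
| 60% | 40% | 51% | 72% | 96% |

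**The case against.** The strongest reply is that Section 8.1.1.6 opens by restating the same objective and can be read as putting [B] into operation. The two texts share survival, dobutamine alone and SVC flow, so calling them incompatible would go too far. That is fair. They still score the same infant differently, and nothing says which prevails.

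A reader might count SVC flow above 55 as a further extra condition. Sections 8.1.1.4 and 8.1.1.5 make it the marker of response and of the effective dose, so it already sits inside *dose success*. At most four criteria are extra, and possibly two.

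A reader might also infer that infants enrolled late succeed by default. The documents do not support this. [B] requires status to be achieved as well as kept, and the primary endpoint ties achievement to scans at 1 and 3 h. An infant starting after 69 h cannot have shown both by 72 h. Under Section 8.1.1.6 a late starter also has less time to reach the thresholds. The gradient in step 4 belongs to the loss rule only.

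The birth clock is a declared choice that matches the indication, transitional circulation in the first 72 h. It is not an error. Detailed handling of missing values is commonly left to an analysis plan, which is not at hand. The protocol itself, however, requires a value that its own schedule makes optional.

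**Conclusion.** The point holds as a contradiction between stated rules. Discordance from [B] success to 8.1.1.6 failure is certain in principle, as the 28-week infant shows. Discordance the other way depends on how *dose success* is read. How often discordance would occur is not known from the documents; the 81–66% (90–81%) range rests on assumed pass rates and independence.

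Unequal time at risk follows from the protocol's own times, but the direction of its effect is clear only for the loss rule. A reader might conclude that the proportion is uninterpretable. That does not follow: it answers the question the objective asks, but it mixes very different exposure times and needs to be read with them. The endpoint is secondary and does not drive dose allocation, so this is a correction that should be made, not one that threatens the primary result.

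**What to change.** - Reconcile footnote [B] (both places), Section 8.1.1.6 and Section 9.1.2 to one definition, chosen by the sponsor before data capture, and state what *dose success* includes. Use it for both the investigator report and the analysis. Which thresholds apply is for the sponsor to decide.
- Report the 72-h criteria as separate components, with unmeasured lactate shown as missing and not as failure.
- Keep the proportion at 72 h from birth, and report it with age at t0 and time at risk.
- Add a supportive analysis of loss of status timed from t0, among infants who achieved it. Follow-up that ends at 72 h from birth depends on age at start, so this analysis should not replace the main proportion.
- Record the clock time of each treatment change. Sections 6.1.2, 6.2 and 8.1.2.2 require changes, concomitant cardiovascular treatment or added support to be recorded, but do not say that times are captured. Section 6.1.2 already provides for recording t0.

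The cost is revised wording, a little more data capture and one further analysis. Sample size and dose allocation are unaffected.
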